### Outcome assessment

See Table 1 for a detailed schedule of assessments. The local research assistant will telephone all patients on POD-30 (± 3 days) to collect responses to the EQ-5D-5L tool. All other outcomes will be collected from the patient’s electronic medical record by blinded members of the study/research team.

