#### Secondary patient-centered outcomes

(i) mean number of allogeneic blood components (ABCs) transfused (including red blood cells, plasma, and platelets) within 24 h of CPB end, with each platelet recorded as 3.5 units based on donor exposure (as 2 buffy coat platelets prepared from 7 donors), (ii) mean number of ABCs within 7 days of CPB, (iii) total number of coagulation factor products administered (fibrinogen concentrate, prothrombin complex concentrates, and activated recombinant factor VII) within 24 h and 7 days of CPB, (iv) incidence of severe to massive bleeding (using a modification of the universal definition of perioperative bleeding [UDPB] in cardiac surgery, and its individual components [34, 35]) within 24 h of CPB, (v) chest tube drainage at 12- and 24-h after chest closure, (vi) total platelet count with a functional platelet count (PlateletWorks) at preoperative baseline, at the time of rewarming on CPB, immediately after CPB at protamine reversal, within 60 min before first product administration, and within 60 min after first product completion, and (vii) changes in international normalized ratio (INR), prothrombin time (PT), activated partial thromboplastic time (aPTT), fibrinogen activity, rotational thromboelastometry (ROTEM) EXTEM clotting time (CT) and maximum clot firmness (MCF), ROTEM FIBTEM MCF and thrombin generation, from within 60 min before to within 60 min after the initiation of the first product administration, (viii) EQ-5D-5L version of EQ-5D™ questionnaire [36] was collected at baseline and at postoperative day (POD) -30, and (ix) case-costing data for each patient.

Additional safety outcomes include (i) incidence of serious treatment-emergent adverse events (AE) from the start of surgery to POD-30, (ii) incidence of thromboembolic events from randomization to POD-30, (iii) duration of ventilation and ventilator-free days up to POD-30, (iv) duration of intensive care unit (ICU) stay up to POD-30, (v) duration of hospitalization up to POD-30, (vi) incidence of death up to POD-30, and (vii) days alive and out of hospital at POD-30.

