### Statistical analysis

For the statistical analysis of the efficacy parameters, the following analysis sets will be considered:

The intention to treat (ITT) population: all randomized patients who receive at least a whole or parts of an IMP dose, irrespective of the number of IMP doses received. We anticipate that ≥ 90% of randomized patients will receive the first dose of IMP. Should a patient receive IMP that is not in concordance with the randomization schedule, the treatment group will be defined according to the randomization (rather than the actual treatment received). The primary outcome and mortality for non-consenting patients will be collected from as many sites as possible, as permitted by the local REB.

The per-protocol (PP) population: all patients in the ITT sample, excluding patients with major protocol deviations. Patients meeting any of the following criteria will be excluded.Patients who do not receive at least 80% of the first platelet dose to which they were randomizedPatients receiving treatment not in concordance with the randomization schedulePatients who significantly violate inclusion/exclusion criteria (e.g., did not have cardiac surgery with CPB, randomized after POD-3, etc.)

The restricted safety population (safety analysis set): all patients who receive at least one whole or parts of the first platelet dose (i.e., the ITT population).

A final decision about the classification of protocol deviations as major and minor and their consequences regarding the assignment of patients to analysis populations will be made during the blinded data review meeting prior to unblinding for the final analyses by the lead PI.

The ITT analysis sample is considered the primary sample for analysis of the primary endpoint. The evaluation of the primary endpoint will additionally be performed for the PP sample.

The data will be analyzed using protocols established for safeguarding privacy and confidentiality. These include password-protected computers, locked file cabinets for hardcopies, and no public discussion of individual cases. There will be no linkages to other datasets, and no disclosures of person identifiers. Reports will present aggregate statistics only.

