### Harms

The condition of the patient will be monitored throughout the study. At each visit, whether scheduled or unscheduled, Adverse Events (AEs) will be elicited using a standard non-leading question. In addition, the Investigator will check the patient records for any documented event. Any AE that occurs during the study will be noted in detail on the appropriate pages of the CRF. The Investigator will grade the severity of all AEs (mild, moderate, or severe), the seriousness (non-serious or serious), and the likelihood that they were related to the administered product (causality). The investigator will also assess the expectedness of each (expected or unexpected). The Investigator will provide detailed information about any abnormalities and about the nature of and reasons for any action taken as well as any other observations or comments that may be useful for the interpretation and understanding of an AE. Importantly, for any AE thought to be related to platelet transfusion, local policies for notifying institutional Blood Banks, Canadian Blood Services, the Transfusion Transmitted Injuries Surveillance System, and the Public Health Agency of Canada will be followed. Transfusion reactions will be classified and graded by the International Society of Blood Transfusion haemovigilance criteria (Standardized definitions | The International Society of Blood Transfusion (ISBT) (isbtweb.org)).

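### The article gives conflicting rules for finding post-discharge events up to POD-30, and names no source for hospital days spent elsewhere

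*Protocol article*

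**What the plan says.** The Outcome assessment section sets a data source for each outcome. For the one follow-up contact it describes: "The local research assistant will telephone all patients on POD-30 (± 3 days) to collect responses to the EQ-5D-5L tool". For the rest: "All other outcomes will be collected from the patient’s electronic medical record by blinded members of the study/research team".

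The safety list under Secondary patient-centered outcomes includes several outcomes that run well past discharge for most patients: "incidence of serious treatment-emergent adverse events (AE) from the start of surgery to POD-30", "incidence of thromboembolic events from randomization to POD-30", death to POD-30, and "days alive and out of hospital at POD-30".

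The Harms section gives a different route for adverse events: "At each visit, whether scheduled or unscheduled, Adverse Events (AEs) will be elicited using a standard non-leading question". It then adds a check of the patient records as a second step. Table 1 marks adverse events, serious adverse events, treatment-emergent events and several blood tests at POD-30.

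The Statistical analysis section, in its privacy paragraph, says: "There will be no linkages to other datasets, and no disclosures of person identifiers".

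**The concern.** An outcome that counts days out of hospital needs every hospital day, wherever it was spent. The Setting section names two academic tertiary centers, so a patient who becomes unwell after discharge may well be admitted somewhere else. If the record searched does not show that stay and nobody asks the patient, those days are scored as days at home.

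The same mechanism could hide a thromboembolic event treated elsewhere. Thromboembolism is the risk that the Interventions and Discussion sections single out for cold-stored platelets, and the Discussion says steps were taken to detect it early. Under the Statistical analysis section, pilot outcome data, including safety data, go into the definitive dataset if that trial proceeds; the Design section makes this conditional on any protocol changes not affecting the definitive primary endpoints. The Background states a hypothesis of non-inferior safety, and missed events make non-inferiority on an absolute scale easier to show. An event that was never collected cannot be recovered later by blinded adjudication.

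**Working it through.** The plan gives no figure on this point to reproduce. The check compares the texts and then illustrates the mechanism with assumed inputs.

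**Step 1. The texts side by side**

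| Place | Rule for events up to POD-30 |
|---|---|
| Outcome assessment | Call for the EQ-5D-5L; all other outcomes from the record |
| Harms | Direct question at every visit, plus a record check |
| Table 1 | Adverse events and blood tests marked at POD-30; no row for readmission |
| Statistical analysis | No linkage to other datasets |

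**Step 2. Two ways a site could follow them**

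- *The call counts as a visit under Harms.* The adverse-event question is asked, so a clot or serious event treated elsewhere can be reported. An admission may surface as a serious adverse event. The number of hospital days elsewhere is still not asked for.
- *The call does not count as a visit.* The caller collects the EQ-5D-5L and stops. Unless there is another POD-30 contact, post-discharge events are known only if they appear in the record.

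The article does not choose between these. Under neither does it state a route to outside hospital days.

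**Step 3. Effect on days alive and out of hospital**

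Recorded value = true value + unrecorded outside hospital days.

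One unrecorded day raises that patient's value by 1. It raises an arm mean by 1/25 = 0.04 day with 25 patients in the arm (50/2), or by 1/22 = 0.045 day with the 22 evaluable patients per arm given under Determination of sample size. How many such days there would be is not in the document.

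**Step 4. Illustration for thromboembolic events**

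This applies only if the call is not treated as a visit and no other contact captures the event. Of the inputs, only N = 50 comes from the document. The assumed ranges are:

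- true event rate p = 5% to 10%;
- share of events occurring after discharge s = 20% to 40%;
- share of those treated elsewhere and absent from the record m = 25% to 50%.

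Expected missed events = N × p × s × m:

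- low end: 50 × 0.05 × 0.20 × 0.25 = 0.125;
- high end: 50 × 0.10 × 0.40 × 0.50 = 1.0.

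Recorded rate = p × (1 − s × m). A true 5% becomes 4.75% (s × m = 0.05) to 4.0% (s × m = 0.20). A true 10% becomes 9.5% to 8.0%.

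**Step 5. Effect on a comparison of arms**

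Let the same fraction L = s × m be lost in both arms. The risk difference becomes (p1 − p0) × (1 − L); the risk ratio p1/p0 is unchanged. For assumed true rates of 10% and 5%, the true difference is 5 points and the ratio is 2.0.

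- L = 0.05: 9.5 − 4.75 = 4.75 points, ratio 2.0.
- L = 0.20: 8.0 − 4.0 = 4.0 points, ratio 2.0.

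Equal loss therefore shrinks the absolute difference and costs precision, but does not distort the ratio in expectation.

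**The case against.** The strongest reply is that the document as a whole does not rely on the record alone for adverse events. Harms requires direct questioning, and Table 1, to which Outcome assessment itself refers for the schedule, marks adverse events at POD-30. Table 1 also lists POD-30 blood tests, which a telephone call cannot supply, so there may be another contact at which the question is asked. This stands. A reader might infer from Outcome assessment that thromboembolism is certain to be undercounted; the document does not support that. It supports a conflict between sections and a possible loss.

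A reader might also infer that a call at POD-27 (30 − 3) cuts the outcome window short. As written, the ± 3 days governs only the EQ-5D-5L, and record-based outcomes run to POD-30 whenever the call is made. The timing matters only once the call collects outcomes.

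Third, the record is not said to be limited to the operating hospital, and the no-linkage sentence sits among privacy measures, so it may not be meant to bar a request for outside records. Both are fair, and both could reduce the loss. Neither provides a route to outside admissions.

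Fourth, this is a condensed article, and call scripts and form questions belong in the full protocol. Their absence is indeed no finding. But the article does not merely omit the source: it states one, and Harms states another.

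Finally, the pilot makes no formal inference on these outcomes, and none of the progression criteria uses them. That limits the weight of the point without removing it.

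**Conclusion.** The point holds as a conflict to be reconciled, together with a gap for days alive and out of hospital. Outcome assessment and Harms (with Table 1) differ on how post-discharge events are found up to POD-30, and no section says how admissions to other hospitals would become known.

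The size cannot be derived from the document. The illustration of roughly 0.1 to 1.0 missed thromboembolic events in 50 patients rests on assumed rates and on the less favorable reading of the call. Any count of patients with unrecorded readmissions would likewise depend wholly on assumed readmission rates and should not be read as an estimate for this trial.

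The loss is expected to be similar between arms as long as blinding holds, and absolute differences then shrink. A reader might infer a bias favoring one product; nothing in the document supports that. The three feasibility endpoints and the planned definitive primary outcome, blood components within 24 h, are unaffected. The point is worth acting on because pilot safety data may be carried into the definitive trial and the correction is cheap.

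**What to change.** Amend Outcome assessment so that POD-30 safety outcomes and days alive and out of hospital come from the record plus the existing call. In that call:

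- ask the non-leading adverse-event question from Harms, and say that the call counts as a visit for that purpose;
- ask about hospital admissions or emergency visits elsewhere since discharge, with dates;
- request the outside records when the answer is yes, and word the no-linkage sentence so that it does not appear to forbid this.

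Once the call collects these outcomes, make it on or after POD-30, for example POD-30 to +3 days, so that it covers the whole window.

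The cost is a few minutes on a call already planned for all patients, an occasional record request and a small change to the case report form. No new visit or procedure is needed.

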### Statistical considerations

The pilot trial will randomize 50 adult (≥ 18 years old) patients undergoing at least moderately complex cardiac surgery with CPB and requiring platelet transfusion. Because the decision to administer platelets occurs intraoperatively but informed consent must be obtained pre-operatively, we will need to consent and enroll a larger sample of approximately 150 eligible patients, as we expect 30–40% of enrolled patients to receive platelets based on historical institutional transfusion practices [23]. This is also the ratio we have observed in similarly designed ongoing RCTs being conducted in this patient population (NCT05523297).

### Determination of sample size

This pilot study will include 50 randomized patients, which, accounting for patients who are randomized but not treated and patients who withdraw in both arms, is expected to provide at least 44 evaluable patients, with 22 in each arm. This sample size of 50 patients allows for sufficiently precise estimates of feasibility outcomes [37] in a reasonable timeline. If fewer than 10% (< 5 patients) receive the incorrect product or receive no product, the upper one-sided 95% confidence limit for this percentage will be ≤ 17.3%. In the 25 patients assigned to cold-stored platelets, if at least 90% have product available, the lower confidence limit will be ≥ 77.7%.

### Statistical analysis

For the statistical analysis of the efficacy parameters, the following analysis sets will be considered:

The intention to treat (ITT) population: all randomized patients who receive at least a whole or parts of an IMP dose, irrespective of the number of IMP doses received. We anticipate that ≥ 90% of randomized patients will receive the first dose of IMP. Should a patient receive IMP that is not in concordance with the randomization schedule, the treatment group will be defined according to the randomization (rather than the actual treatment received). The primary outcome and mortality for non-consenting patients will be collected from as many sites as possible, as permitted by the local REB.

The per-protocol (PP) population: all patients in the ITT sample, excluding patients with major protocol deviations. Patients meeting any of the following criteria will be excluded.Patients who do not receive at least 80% of the first platelet dose to which they were randomizedPatients receiving treatment not in concordance with the randomization schedulePatients who significantly violate inclusion/exclusion criteria (e.g., did not have cardiac surgery with CPB, randomized after POD-3, etc.)

The restricted safety population (safety analysis set): all patients who receive at least one whole or parts of the first platelet dose (i.e., the ITT population).

A final decision about the classification of protocol deviations as major and minor and their consequences regarding the assignment of patients to analysis populations will be made during the blinded data review meeting prior to unblinding for the final analyses by the lead PI.

The ITT analysis sample is considered the primary sample for analysis of the primary endpoint. The evaluation of the primary endpoint will additionally be performed for the PP sample.

The data will be analyzed using protocols established for safeguarding privacy and confidentiality. These include password-protected computers, locked file cabinets for hardcopies, and no public discussion of individual cases. There will be no linkages to other datasets, and no disclosures of person identifiers. Reports will present aggregate statistics only.

In the pilot study, we will estimate rates and percentages for feasibility outcomes, along with lower one-sided 95% CIs where high percentages are desirable (e.g., enrollment rate) and upper one-sided CIs where low percentages are desirable (e.g., loss to follow-up, protocol deviations). Point estimates will be compared to our predetermined targets to make decisions on feasibility and the need for changes to the protocol.

Although this study will make no formal inferences on the definitive trial's primary and secondary outcomes, we will present outcomes in tables and graphs (e.g., a histogram for DAOH-30). The differences in means or percentages between the intervention and control groups will be estimated, along with a parametric or bootstrapped (for DAOH) 95% CIs.

The feasibility outcomes of the pilot study will inform the conduct of the definitive trial. Specifically, if all 3 of our primary feasibility outcomes are achieved, we will proceed to a larger trial with minimal or no protocol modifications. If only a portion of our primary feasibility outcomes are achieved, we will hold an investigator meeting and ascertain what aspects of the protocol should be modified, and if a second pilot trial is required in the face of significant protocol modifications prior to proceeding with a larger trial. If none of our primary feasibility outcomes are achieved, we are unlikely to be able to proceed with a larger trial [33, 38]. If we proceed to the definitive trial, all outcome data derived from the pilot study pertaining to the definitive trial’s primary, secondary, and safety outcomes will contribute to the definitive trial's dataset.

No interim analysis will be conducted. We will assess enrollment, randomization, and treatment rates by sex and institution but, because of the small sample size, analyses of the pilot study will not examine subgroups. In the main study, heterogeneity of treatment effect will be assessed by examining possible interaction effects by sex (male/female) and surgical complexity (simple/complex surgery).

### Data management and auditing

The Anesthesia Clinical Trials Unit at Toronto General Hospital will serve as the study coordinating center. Source records will be preserved for the maximum period of time required by local regulations. Authorized study staff (e.g., sub-investigators, clinical research coordinators/assistants, nurses) will enter study data into an electronic case report form (eCRF) for each patient enrolled as documented in the Delegation of Authority Log. A validated institutional REDCap interface will be used. Monitors will perform source data verification (SDV). Discrepancies and queries can only be corrected by the Investigator(s) or other authorized site personnel. Manual checks will be performed and programs run throughout the study until the data is clean and the database is ready for lock. All discrepancies will be resolved prior to database lock. There will be a final run of the programmed checks to ensure all discrepancies are closed out, SDV will be confirmed as complete by the monitor, and all eCRFs will be approved by the Investigator prior to database lock.

### Monitoring and auditing

We will employ an Independent Data Safety Monitoring Committee (IDSMC) tasked with ensuring participant safety. The IDSMC will be independent of the study sponsor and competing interests. If any study findings demonstrate concerns regarding platelet quality, efficacy, or safety, an investigator meeting will be held to review the next steps, which may include an additional meeting of the IDSMC. The Investigator will make all study-related source data and records available to a qualified quality assurance auditor or REB and regulatory inspectors, after reasonable notice.

### Harms

The condition of the patient will be monitored throughout the study. At each visit, whether scheduled or unscheduled, Adverse Events (AEs) will be elicited using a standard non-leading question. In addition, the Investigator will check the patient records for any documented event. Any AE that occurs during the study will be noted in detail on the appropriate pages of the CRF. The Investigator will grade the severity of all AEs (mild, moderate, or severe), the seriousness (non-serious or serious), and the likelihood that they were related to the administered product (causality). The investigator will also assess the expectedness of each (expected or unexpected). The Investigator will provide detailed information about any abnormalities and about the nature of and reasons for any action taken as well as any other observations or comments that may be useful for the interpretation and understanding of an AE. Importantly, for any AE thought to be related to platelet transfusion, local policies for notifying institutional Blood Banks, Canadian Blood Services, the Transfusion Transmitted Injuries Surveillance System, and the Public Health Agency of Canada will be followed. Transfusion reactions will be classified and graded by the International Society of Blood Transfusion haemovigilance criteria (Standardized definitions | The International Society of Blood Transfusion (ISBT) (isbtweb.org)).

### Ethics and dissemination

This study will be conducted in accordance with the ethical principles laid down in the Declaration of Helsinki. The study protocol and any subsequent amendment(s) will be submitted to an REB and to Health Canada. Following approval by Health Canada and the hospital Research Ethics boards, patients will be fully notified about potential risks as part of the informed consent process well before surgery. Eligible patients will be approached by a research coordinator in surgical preadmission clinics for written informed consent. The Investigator will ensure that the patient’s confidentiality is preserved. On CRFs or any other documents submitted to the Sponsor, the patients will not be identified by their names, but by a unique patient identifier. Documents not intended for submission to the Sponsor (e.g., the confidential patient identification code list, original consent forms, and source records) will be maintained by the Investigator in strict confidence. Only the Investigator and statistical team will have access to the final trial dataset and in the event of safety concerns the members of the IDSMC. The results of this study will be published and may be presented at scientific meetings. Authors meeting the International Committee of Medical Journal Editors Guidelines for authorship will be included in relevant publications. Due to the small sample size and potential patient identifiers in the dataset, no additional access to patient-level data will be granted outside of the study team. Any protocol amendments will be communicated to the REB, IDSMC, trial registries, and individual participants.

